Given the evidence for multimodal interventions in general [27, 44] and for specific components of DNK, we expect positive effects of DNK. In the present study a parallel-group randomized controlled trial (RCT) will be conducted. The first aim is to examine the effectiveness of DNK compared to care as usual (CAU) in terms of (1) reducing recidivism and (2) improving self-sufficiency as primary outcomes and in terms of (3) improving quality of life, (4) attending school/work, (5) improving psychological functioning, (6) reducing cognitive distortions and (7) reducing substance use as secondary outcomes. The secondary outcome measures are important objectives of DNK and (indirect) outcomes of the intervention. The second aim of this study is to obtain insight into the development of the primary and secondary treatment outcomes over time and to explore potential moderating effects. Potential moderators are participant and program characteristics, including program integrity. The third aim is to calculate the societal costs by conducting a cost-effectiveness analysis.

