Since the effectiveness of interventions can differ between various subgroups, the second aim of our study is to investigate several participant and treatment characteristics as potential moderators in order to investigate for whom DNK may work [50]. Regarding participant characteristics, we consider demographic factors, intellectual functioning [51, 52], criminal history [28, 53] and motivation for treatment [54] as moderators because it has been argued that these characteristics may account for different intervention effects in forensic populations. Moreover, we will examine the predictive value of nonspecific program factors, such as group climate (until now mostly examined in secure settings) [55–58] and therapeutic relationship (until now mostly examined in the field of psychotherapy) [59–62]. Finally, program integrity – the extent to which a program is implemented as intended [63, 64] – will be evaluated as the quality of implementation is strongly related to the effectiveness of an intervention [28, 42, 63]. Without determining whether important characteristics of the DNK program are conducted as prescribed in the protocol, there is a risk of unjustly concluding that DNK is not effective while it might not have been fully implemented, or that the intervention seems effective while the actual execution differs from the original protocol.

For policy-makers, who strive to find a balance between effects of interventions and associated costs, it is important to gain knowledge about the societal costs of interventions [65]. Including measures of cost-effectiveness in our study can provide important information for policy as the resources to fund interventions are scarce. However, currently, not much is known about cost-effectiveness in the field of (youth) mental health care and, to the best of our knowledge, it has not been assessed in interventions for multi-problem young adults.

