### Aims of the study

The first aim of this study is to examine the effectiveness of the multimodal day treatment program DNK compared to CAU (i.e., interventions to which young adults are referred by the social welfare agency in Rotterdam) in terms of official and self-reported delinquency (recidivism) and self-sufficiency. Secondary outcomes are quality of life, attending school or work, psychological functioning, cognitive distortions and substance use. The second aim of this study is to obtain more insight into the development in time of the abovementioned primary and secondary treatment outcomes and to assess to what extent *participant characteristics* (i.e., demographic factors, intellectual functioning, criminal history and motivation for treatment) and *program characteristics* (i.e., duration, intensity and type of intervention, therapeutic relationship, group climate, and staff characteristics) influence this development to treatment success or failure. Another important program characteristic regarding the effects of DNK will be the extent to which program integrity is met. The third aim of this study is to estimate the societal costs of multi-problem young adults and to compare the cost-effectiveness of DNK and CAU. This study will contribute to the scant knowledge about what works for whom regarding a heterogeneous, multi-problem young adult group.

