Multi-problem young adults aged between 18 and 27 years will be recruited after their first interview at the social welfare agency in Rotterdam. After informed consent is obtained, baseline measurement (T0) will take place. After T0, the random assignment (with a ratio between DNK and CAU of 1:1) will be carried out by the first author. The random allocation is determined via an online computer program for randomization (www.random.org). Subsequently, the randomization numbers will be kept in sealed envelopes at the social welfare agency. During the baseline measurement the participant, researcher and youth coach will still be blind to the treatment condition. The first author will inform the youth coach about the outcome of the randomization. Only at the second interview will the young adult be informed by the youth coach about the assignment to the treatment or control condition. During the phase between the first and second interviews, the so-called statutory effort period, no intervention takes place. Only the participants who return for a second interview can be referred to an intervention. Therefore, participants who do not return within the run-in period will be excluded from the analyses. In this way, the statutory effort period is considered as a run-in period [74, 75] to deal with the estimated dropout rate of approximately 40% (p. 9) during this period [71]. Although some researchers have pointed out that a run-in period may influence the generalizability of the results [74, 76], it will improve the internal validity – the primary condition for valid outcomes – of our study [77]. Of the subjects who will be excluded during the run-in period, data will be collected at the follow-up measurements to compare the outcomes of the included and excluded groups and to incorporate this in generalizations from the study [74]. Figure 1 shows the flowchart of this study and Fig. 2 shows the SPIRIT schedule of enrollment, interventions and assessments.

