*T0* baseline measurement; *T1* follow-up at 2 months after start intervention (adherence) or 4 months after T0 (nonadherence); *T2* follow-up at 8 months after T0; *T3* follow-up at 14 months after T0; *Ts* measurement of SSM-D at start intervention; *Te* measurement of program integrity and WAV at the end of intervention (only in the experimental group). *Y* young adult, *P* professional, *F* files/register information, *R* researcher. *ASR* Adult Self-report, *DNK* De Nieuwe Kans, *HIT* How I Think questionnaire, *GCI* Group Climate Inventory, *MANSA* Manchester Short Assessment of Quality of Life, *MATE* Measurements in the Addictions for Triage and Evaluation, *SCIL* Screener voor intelligentie en licht verstandelijke beperking, *SRD* Self-report Delinquency Scale, *SSM-D* Self-Sufficiency Matrix – Dutch version, *VMB* Motivation for Treatment Questionnaire–Short Form, *WAIS-III SF* Wechsler Adult Intelligence Scale - Short Form (third version), *WAV* Werk Alliantie Vragenlijst

^a^These questionnaires are only filled out when the respondent follows the program or has just finished it. ^b^DNK professionals only fill out the WAV at T*e.*
^c^This questionnaire will be filled in twice a year for a total of 4 times

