To gain more insight into the possible differences between DNK and CAU in the development of the primary and secondary treatment outcomes up to and including T3, additional analyses will be conducted by means of mixed-model analyses for the continuous outcome measures (i.e., recidivism, self-sufficiency, quality of life, psychopathology, cognitive distortions and substance use) and Generalized Estimating Equations (GEE) for the categorical outcome measure *work/school*. In these analyses, the outcome data of T0, T2 and T3 will be included. T1 data are excluded from the analyses since T1 is an additional assessment point to measure treatment characteristics and, therefore, not all primary and secondary outcomes are included at T1. In the mixed-model analysis *treatment condition* and *time* (i.e., the assessment point: T0, T2 or T3) will be set as fixed factors, and the participants as a random effect. By analyzing the interaction between treatment condition and time, differences between both groups in development over time can be examined. If the overall interaction is significant, post-hoc analyses will be conducted to investigate at which time point the differences can be found. A similar analysis will be conducted with GEE, using an unstructured correlation matrix to account for within-subject correlations due to repeated measures.

Subsequently, moderator analyses will be carried out by the addition of potential moderators as covariates (in case of continuous variables) or as factor (in case of the categorical variable work/school) to the abovementioned mixed-model and GEE analyses. A three-way interaction between treatment condition, time and moderator will give insight into the influence of a moderator on the development in outcome between DNK and CAU. Post-hoc analyses will be carried out if the model appears to be significant. Moderators regarding registered recidivism will be examined with Cox regression analyses (a two-way interaction between treatment condition and the moderator).

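### The moderator tests take in variables measured after randomisation and only in programme attenders (motivation, climate, alliance), and one measured only in DNK (program integrity)

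*Protocol article*

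**What the plan says.** **The tests.** The Statistical analysis section adds the potential moderators to the mixed models and GEE: "A three-way interaction between treatment condition, time and moderator will give insight into the influence of a moderator on the development in outcome". For official records it says "Moderators regarding registered recidivism will be examined with Cox regression analyses (a two-way interaction between treatment condition and the moderator". Neither sentence separates moderators by timing or by arm.

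**What counts as a moderator.** The Background states "Potential moderators are participant and program characteristics, including program integrity", and for participants "we consider demographic factors, intellectual functioning [51, 52], criminal history [28, 53] and motivation for treatment [54] as moderators". Aims of the study lists the program characteristics as "duration, intensity and type of intervention, therapeutic relationship, group climate, and staff characteristics", and then adds program integrity.

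**When and in whom they are measured.** The Design section says "After T0, the random assignment (with a ratio between DNK and CAU of 1:1) will be carried out by the first author", so T1 and T2 follow randomisation. In Table 1 (Instruments) VMB, GCI and WAV have no T0 entry; they appear at T1 and T2. Footnote a says of these three: "These questionnaires are only filled out when the respondent follows the program or has just finished it". The Table 1 legend defines Te as "measurement of program integrity and WAV at the end of intervention (only in the experimental group". The section on program integrity confirms that its participant questionnaire is completed at the end of a DNK trajectory by the participant and his coach.

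**The concern.** An interaction between randomised arm and a moderator keeps the protection of randomisation only if allocation cannot have changed the moderator or decided who has a value for it. Three kinds of variable in this plan fall short.

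- **Motivation** is classed as a participant characteristic. Yet the Background and the description of the experimental condition make building motivation a goal of DNK, particularly in its first phase. A score taken two months into the programme may be partly an early treatment response.
- **Climate and alliance** describe the programme a man ended up in and are recorded only while he attends.
- **Program integrity** has no counterpart in CAU.

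At stake is the second aim, which asks for whom DNK works. An association between early engagement and outcome could be reported as a difference in benefit between types of participant.

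**Working it through.** The plan gives no figure for the moderator tests, so there is none to reproduce. There are two checks: whether the term can be estimated at all, and how far the test can depart from 5% when it can.

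**1. Estimability**

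Let A be arm (DNK = 1), t2 and t3 indicators for T2 and T3 (the model uses T0, T2 and T3), and M the moderator. The full three-way model has 12 columns: 1, A, t2, t3, M, A·t2, A·t3, A·M, M·t2, M·t3, A·M·t2, A·M·t3.

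- M observed in both arms: rank 12 of 12, estimable.
- M only in DNK, CAU coded 0: A·M = M, A·M·t2 = M·t2 and A·M·t3 = M·t3. Three columns are duplicates, so the rank is 12 − 3 = 9.
- M only in DNK, CAU missing: A = 1 throughout. Only 1, t2, t3, M, M·t2 and M·t3 are distinct, so the rank is 6.

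For program integrity and the Te WAV no interaction with arm can therefore be separated from the moderator's own effect. This needs no assumed value. Table 1 does not restrict VMB, GCI or the participant WAV at T1 and T2 to DNK, so the first case applies to them, among attenders.

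**2. Size of the test for a post-randomisation moderator**

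Assume no true moderation by pre-treatment motivation. Let the T1 score track outcome with standardised slope b1 in DNK and b0 in CAU, because it reflects early response more in one arm. With n attenders per arm:

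z = (b1 − b0) / √[(1 − b1²)/n + (1 − b0²)/n]

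rejection rate = Φ(z − 1.96) + Φ(−z − 1.96)

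Example, 0.5 v 0.2 and n = 60: z = 0.3 / √[(0.75 + 0.96)/60] = 0.3 / 0.169 = 1.78, giving Φ(−0.18) ≈ 43%.

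| Assumed slopes, DNK v CAU | n = 60 | n = 100 |
|---|---|---|
| equal | 5% | 5% |
| 0.3 v 0.2 | 9% | 11% |
| 0.4 v 0.2 | 21% | 32% |
| 0.5 v 0.2 | 43% | 63% |

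The documents give neither slopes nor attender numbers; both are assumptions. The upper n equals the approximately 100 per condition in the Power analysis section.

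**3. A second illustration with other assumptions**

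This is a simulation of 300 men (4,000 runs), with a common treatment effect of 0.40, no true moderation and a single outcome time.

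- Baseline moderator: mean interaction 0.00, rejection 5.7%.
- Post-randomisation moderator tied more strongly to prognosis in DNK: mean interaction 0.10, rejection 12.1%.
- Attenders only, with selection differing by arm (about 193 of 300 retained): mean interaction −0.05, rejection 6.5%. The arm difference among those retained is 0.57 instead of 0.40.
- Both mechanisms together: mean interaction 0.05, rejection 6.7%, because here they pull in opposite directions.

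**4. Timing in the Cox model**

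Under Primary outcomes, observation of recidivism starts at T0. Instruments puts programme start about 2 months after intake and T1 a further 2 months on. A moderator value therefore exists only about 4 months into follow-up, and only for men still attending or just finished.

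**The case against.** **The article partly says what is wanted.** The Background speaks of examining how well climate and the therapeutic relationship predict outcome, which is close to an associational analysis. Table 1 puts program integrity under its own heading, outside both moderator blocks, and the Discussion presents it as insight into how DNK works. A three-way test of integrity comes from combining the Background's list with the Statistical analysis section; no single sentence states it. This stands as mitigation. Even so, the Background names integrity as a moderator and the analysis section makes no exception, so the two need reconciling.

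**The inflation figures depend on chosen slopes.** This stands. A reader might take 43–63% as the expected error rate. The documents do not support that: equal slopes give 5%, and the formula compares slopes at one time point and is not the planned repeated-measures test.

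**Most moderators are not DNK-only.** This stands. A reader might infer that none of the program-related interactions can be estimated. Only program integrity and the Te WAV are marked as experimental-group only.

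**Missing values in non-starters.** A man in no programme has no group climate or alliance to measure, so for GCI and WAV the gap is a matter of definition. That supports treating them as within-programme predictors.

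**WAIS-III SF.** It is also taken at T1, so a reader might want it removed. It carries no attendance footnote, and intelligence is a fairly stable trait, so treatment-induced bias is likely to be small.

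**The aim is exploratory.** True, and this limits the severity. That DNK referrals would be misdirected is conjecture.

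**Conclusion.** The point holds in three graded parts.

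- **Cannot be estimated:** the interaction of arm with program integrity or with the end-of-programme WAV. This follows from the measurement schedule alone.
- **Can be estimated, but outside the randomised comparison and exposed to bias:** the interactions of arm with motivation, group climate and alliance at T1 or T2. False positives run from the nominal 5% upward. How far depends on how differently the two arms shape the scores and the attendance, which the documents do not tell us. All slopes and attender counts used above are assumptions.
- **Sound:** demographics, SCIL and criminal history, which are available before randomisation.

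A reader might infer that the trial's main result is affected. It is not: the primary T3 comparison uses none of these variables. This should be corrected before the moderator analyses are run, but it does not threaten the main conclusion.

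**What to change.** Change the wording of the moderator paragraph in the Statistical analysis section:

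1. Restrict treatment × time × moderator tests, and the Cox treatment × moderator test, to characteristics fixed before randomisation: demographics as recorded at T0 (Table 1 repeats that questionnaire later), SCIL, and criminal history from the lifetime SRD and judicial records before T0.
2. Keep WAIS-III SF as a fairly stable trait, stating that it is measured at T1.
3. Exclude program integrity and the Te WAV from any interaction with arm, and align the Background sentence that calls integrity a moderator.
4. Analyse VMB, GCI, WAV and program integrity as within-arm predictors among attenders, labelled associational, in line with the Background's interest in climate and alliance as predictors. Report how many men in each arm supplied a value.

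No new data are needed. The cost is that the trial makes no randomised moderation claim for motivation, climate or alliance. Trial status reports that recruitment has finished, so a T0 motivation score can no longer be collected.

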## Discussion

This article describes the design of the effect study on New Opportunities (in Dutch: De Nieuwe Kans; DNK), a multimodal day treatment program in The Netherlands for multi-problem young adults (aged 18–27 years). Considering the severity and persistence of their problems and considering the fact that many mental health care services for juveniles and the juvenile justice system stop offering support around the age of 18–21 years, effective interventions are urgently needed for these young adults in the complex transition to adulthood. This study protocol describes the design of an RCT in clinical practice to examine the (cost-)effectiveness of DNK in comparison with care as usual (CAU). Moreover, this study will explore the development of the outcomes over time, and the role of participant and program characteristics in order to be able to answer the question: What works for whom and under which circumstances?

The present study has several strengths. First, to our knowledge, this is one of few RCTs examining a multimodal day treatment program, not being an aftercare program, for multi-problem young adults. This RCT will contribute to the knowledge about effective interventions for these young adults, who are urgently in need of effective care. The randomization allows us to control for confounding variables more accurately than other (quasi- or nonexperimental) study designs [45, 116, 117]. Moreover, this trial takes place in everyday clinical practice and thus meets the needs of professionals, policy-makers and politicians and yields results of high ecological validity [67] which often attracts limited attention in RCTs [118, 119].

Secondly, we will adopt a broad perspective regarding treatment outcomes. Self-sufficiency – consisting of various life domains – as a primary outcome, in addition to recidivism, may lead to a more holistic view of the effects of interventions on other aspects of the lives of multi-problem young adults than solely delinquency. To our knowledge, self-sufficiency has not yet been used as an outcome measure in large-scale scientific research. Moreover, we shall approach recidivism from different points of view; namely, time to relapse (recorded), frequency and seriousness of delinquency (self-reported and recorded). Additionally, we include a wide range of secondary outcomes. This broad perspective regarding treatment outcomes fits well with the heterogeneity of our sample.

Thirdly, we will use a wide range of instruments and we will gather information from multiple sources (both self-reported and registered; from participants and professionals) about the young adults, the participating interventions and the context in which the programs are carried out. Information about general program factors could give further information about their contribution to intervention effects [120] and data about program integrity might give some insight into *how* DNK works. Moreover, we will also include the participants who drop out before or during intervention in our extensive follow-up measures. This will give insight into the consequences of the formal procedures preceding intervention and may eventually enable us to describe profiles of treatment success and failure.

Finally, in addition to the participant and program characteristics, cost-effectiveness will be examined. This topic has recently gained more interest due to changes in the health care system and payment plans [65, 121]. To our knowledge a questionnaire or standard procedure to measure cost-effectiveness for a multi-problem young adult group is not yet available. Therefore, the first author developed a questionnaire for this target group, based on the Trimbos/iMTA questionnaire for Costs associated with Psychiatric Illness (TiC-P) [107], to enlarge the knowledge regarding their societal costs.

Despite the strengths of this study, several pitfalls might threaten the quality of our study. A great challenge will be realizing an adequate response rate at baseline and follow-up measurements. As our target group often has an extensive history of youth care and criminal justice services, they may have negative experiences with formal help and are reluctant to make an appeal to these services again [4]. Moreover the participants probably have completed questionnaires on a regular basis within the context of diagnostic tests or examinations. Therefore, they may have become tired of questionnaires or suspicious about their purposes [80]. To keep the nonresponse rate as low as possible, the research team will be well trained, outreaching, attentive, flexible and will give clear information about the content, goals and procedures of the study to the participants. As it could be difficult to trace them for follow-up measurements – because of many changes in telephone numbers, addresses and social network [80] – we will put much effort in maintaining contact with the respondents (e.g., by making contact via calls, Whatsapp, Short Message Service (SMS), e-mail and Facebook; by contacting their families and third parties; and by visiting them at home).

Another possible threat to the value of our study is the risk of nonadherence to interventions (i.e., risk of dropout of *treatment*) due to the combination of multiple problems in the lives of these young adults, the difficult referral path from intake at the social welfare agency to start at the interventions, and the early moment of randomization [79, 80]. Unfortunately, it is not possible to conduct the randomization in a later stage as a consequence of legal requirements. However, the advantage of this situation is that the referrers will be involved in the randomization process [79] and we will fit in with the guidelines of pragmatic trials (i.e., staying close to normal practice and obtaining insight into the whole target group) [67]. To prevent the study from showing a distorted view due to large dropout during the statutory effort period at the social welfare agency, a run-in period has been created: only participants who return at the end of the effort period will be included in the analyses for the examination of the effectiveness of DNK.

Finally, an active control group (i.e., CAU) might lead to smaller effect sizes than when DNK would be compared to no treatment or a wait-list group. However, considering the seriousness of the problems of these emerging adults it would not be ethical to let them wait for an intervention.

In conclusion, with the present design we are able to examine what the added value is of DNK in comparison to CAU, which could provide important information for referrers, policy-makers and politicians. This study will contribute to the knowledge, which is still very limited, about what works for multi-problem young adults. The study design, specifically, may give insight for other researchers into implementing an RCT in the dynamic setting of daily clinical practice for this complex target group.

